### Safety monitoring and adverse events

We are not anticipating any adverse events as part of this intervention which is an earlier provision of a routine intervention, thus we will not record any as part of this study. However, we will collect information from participants, including hospital admissions and falls during all follow-up visits. As this is a feasibility trial, we will not convene a data monitoring committee. A trial advisory group is in place and includes experienced researchers, social care staff, third sector groups and public and patient representatives.

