## Introduction

### Background and rationale

An adaptation is defined as ‘any permanent alteration to a building carried out with the intention of making the building more suitable for a disabled person’;^1^ internationally, these may be referred to as ‘home modifications’.^2^ Bathing adaptations usually involve the removal of a bath and replacement with an accessible showering facility and are the most commonly requested adaptation.^3^ The Care Act 2014^4^ has placed a responsibility on local authorities to provide services which prevent or delay the need for care and support. In a review of national and international evidence on prevention in older people's services, Allen and Glasby^5^ reported that housing adaptations were 1 of the 10 ‘most promising’ interventions. They reported that housing adaptations can lead to: improved quality of life, reduced use of care services (such as homecare), postponed entry into residential care and reductions in falls. They are thus potentially associated with significant cost savings and better, preventive, outcomes for users and carers. However, despite the inclusion of housing adaptations in this review, the findings from studies that have investigated their effects are equivocal.

Major adaptations to bathing facilities are indicated when a person is unable to access the bath safely and/or independently and are recommended by occupational therapists when other bathing equipment is unsuitable. Removal of the bath and replacement with an accessible shower usually costs between £3000 and £4000; in England and Wales, a means tested government grant, the Disabled Facilities Grant (DFG), is available to assist with the cost of these adaptations.^6^ However, there are often lengthy delays^7^ and in local authority areas, waiting times can be in excess of 1-year and sometimes up to 2 years.^8^ Delays in provision of adaptations are reported to increase the risk of falls, hospitalisation^9^ and lead to increased costs due to further care being required during the wait.^10^ Care and Repair England^11^ have estimated that a delay of 1-year in providing a housing adaptation to an older person can increase homecare costs by £4000; this is comparable with the cost of providing a bathing adaptation. A recent survey revealed that 96% of occupational therapists believed that adaptations led to reductions in the need for social care services.^8^ It is seemingly counterintuitive to delay such interventions.

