### Outcomes

The main outcome for the study is to determine the feasibility of conducting a larger, powered study. This will be a composite of: whether the eligibility criteria are realistic; whether users and carers are willing to be randomised; the study attrition rate; whether the adaptations can be completed within 4–6 weeks of allocation to a project officer (in both groups); the suitability and sensitivity of outcome measures; the most suitable outcome measure for use in the main study; the feasibility of collecting the data on costs and health and social care use.

The service user outcomes to be assessed, at 3 and 6 months postrandomisation, will be: health and social care-related quality of life, perceived physical and mental well-being, personal ADL, independence in bathing, perceived difficulty in bathing, perceived risk of falling, falls, number of care support hours, health and social care service usage. The outcome measures which will be used are: EuroQol EQ5D-5L,^20^ Adult Social Care Outcomes Toolkit (ASCOT),^21^ Short-Form 36 (physical and mental component summaries),^22^ Barthel index^23^ (bathing question analysed as a separate outcome), 0–100 scale for perceived difficulty in bathing and the Falls-Efficacy Scale.^24^ A purposely designed questionnaire will gather information on the use of other health and social care services, with particular emphasis on the use of homecare and residential care.

The carer outcomes to be assessed, at 3 and 6 months postrandomisation, will be: health-related quality of life, perceived physical and mental well-being and caregiver strain. The outcomes measures which will be used are: EuroQol EQ5D-5L,^20^ Short-Form 36 (physical and mental component summaries)^22^ and Caregiver Strain Index.^25^ We will also gather data on the carers' use of health and social care services. The timeline and proposed flow of participants through the study is shown in figure 1.

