### Concomitant treatments

There are no known issues with concomitant treatments and no treatments will be excluded. It is expected that participants in both groups will receive a range of input from other health and social care services. Information will be kept on the participant's use of other acute and community services and will be reviewed as part of the health and social care resource use data.

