### Data collection, management and analysis

Data will be collected in the participants' homes on a paper case report form (CRF) and will subsequently be entered onto a secure password protected, purposely designed electronic Microsoft Access database. Outcome data will be entered by the research assistant who collected the data (thus will be entered blinded to treatment allocation). Each participant will be assigned a trial identity code number, allocated at randomisation, for use on CRFs other trial documents and the electronic database.

CRFs will be treated as confidential documents and held securely in accordance with regulations. The investigator will make a separate confidential record of the participant's name, date of birth, local social care number and participant trial number to permit identification of all participants enrolled in the trial, in accordance with regulatory requirements and for follow-up as required.

When data collection is complete, a data quality check will be conducted in duplicate by two researchers and a 10% sample of the database will be checked against the original paper CRF. Steps will be taken to minimise missing data by personal contact throughout the study period from the investigator and every attempt will be made to locate participants for follow-up. Outcome data will be collected in person by a research assistant to minimise the amount of missing data. For each outcome measure used where data are missing, an imputed average will be used for items where <10% of the overall measure is missing. Where more than 10% of a measure is missing, the entire measure will be coded as missing, unless the scoring criterion for that measure stipulates an alternative approach. We will not collect any further data for participants who withdraw from the study, but we will retain all data collected up until the point of withdrawal.

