The main end point for the study is to determine the feasibility of conducting a larger, powered study. Descriptive statistics will be used for this analysis, based on analysis of the trial screening and recruitment log, loss to follow-up, and analysis of the qualitative interview data. Analysis of outcome data will be by intention to treat, and participants will be analysed according to their treatment assignment irrespective of whether they completed the treatment. It will not be possible to collect any outcome data for those who discontinue participation in the study. The data collected from the outcome measures in the trial will be presented using summary statistics and any differences between the arms will be calculated at 3 and 6-month follow-ups, along with the 95% CIs. These data will be used to inform a sample size calculation, treatment effect estimate and to determine the appropriateness of these measures for use in a larger, powered study. Assistance from a statistician will be available as required.

The pilot economic analysis will be conducted from a health service and societal perspective. It will measure service user outcomes using the EQ5D-5L and use clinical outcomes where appropriate. Detailed resource costing will be undertaken from a health and social care service, user and societal perspective. As such, a cost profile will be calculated for each arm of the trial. This will enable the study results to be reported in terms of cost utility and cost-effectiveness. An incremental cost-effectiveness ratio (ICER) and cost-effectiveness acceptability curves (CEACs) will be produced for the intervention versus usual care, including the joint uncertainty in differential costs and effects from the cost-effectiveness plane. The ICER provides a ratio measure of increment costs and effects of the intervention over usual care. The CEAC use probabilistic analysis to provide a measurement of probability or thresholds showing the various levels of confidence from 0 to 100 (0–1 in terms of probability) of the intervention being cost-effective at a given cost. It should be noted that any reporting of such data in this study are only a guide to any future potential evaluation and it is the proof and testing of the methods that will be the main focus of the health economic analysis not the final results in themselves.

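### The rule that no adverse events will be recorded overlooks the waiting arm and leaves deaths, injuries from the works and events that prompt withdrawal with no stated recording

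*Protocol article*

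**What the plan says.** The Safety monitoring and adverse events section gives its reason first: "We are not anticipating any adverse events as part of this intervention which is an earlier provision of a routine intervention". It draws the conclusion directly: "thus we will not record any as part of this study". It then qualifies this: "we will collect information from participants, including hospital admissions and falls during all follow-up visits". There is no data monitoring committee, but a trial advisory group is in place.

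Four other places bear on the point:

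- Background and rationale: "Delays in provision of adaptations are reported to increase the risk of falls, hospitalisation".
- Outcomes: the service user outcomes at 3 and 6 months include "perceived risk of falling, falls, number of care support hours, health and social care service usage". The service-use questionnaire puts particular emphasis on homecare and residential care.
- Concomitant treatments: "Information will be kept on the participant's use of other acute and community services".
- Data collection, management and analysis: for outcome data, "any differences between the arms will be calculated at 3 and 6-month follow-ups, along with the 95% CIs". The same section says "We will not collect any further data for participants who withdraw from the study", and adds that outcome data cannot be obtained from those who discontinue.

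**The concern.** This is a stated rule with a stated reason, not a detail left to a fuller document. The reason is weak in two ways. First, whether an event is anticipated does not settle whether it should be recorded, because unanticipated harms can be seen only if someone writes them down. Second, it looks only at earlier provision. The trial compares that with a wait of about 3 months before planning starts, and the article's own rationale attaches harm to waiting.

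The rule also sits awkwardly beside the sentence that follows it. A reader cannot tell whether falls and admissions count as harms, or how any other untoward event in these adults aged 65 or over would be captured.

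At stake are the safety information from this study, the completeness of the falls, admission and cost data, and a rehearsal of adverse-event capture before a powered trial. Attrition and the feasibility of collecting service-use data are part of the main outcome, so a gap that arises at withdrawal bears on what the study is meant to learn.

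**Working it through.** No arithmetic applies. The article gives no rate for falls, admissions, deaths or other adverse events, and no formal sample size calculation that depends on one. The check is to take each kind of event and ask where the article provides for it.

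| Event | Provision for recording | Comparison by arm |
|---|---|---|
| Fall, participant seen at a later visit | Outcomes; Safety monitoring | Implied by the planned between-arm differences |
| Hospital admission, participant seen at a later visit | Safety monitoring; Concomitant treatments; service-use outcome | Implied, as above |
| Residential-care use, participant seen at a later visit | Service-use questionnaire (Outcomes) | Implied, as above |
| Death | None stated | None stated |
| Injury linked to the works, with no fall or admission | None stated as an injury; at most it shows up as a service contact | None stated |
| Event that prompts withdrawal before the next visit | None stated; collection stops at withdrawal | None stated |

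**Rows 1 to 3.** The two harms that the Background section links to delay are both collected, in both arms, at every follow-up visit. The analysis text speaks of data from the outcome measures and does not name counts of falls or admissions. Their comparison by arm therefore follows from the outcome list but is not spelled out.

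**Row 4.** Falls and admissions are to be collected from participants at visits. That route cannot report a death. A death would presumably count towards loss to follow-up, which is described, but nothing says it is recorded as an event.

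**Row 5.** The intervention usually involves taking out a bath and fitting a level-access shower. A fall or admission during that work would be picked up at the next visit. Another injury would not be recorded as one.

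**Row 6.** Someone who falls, is admitted and then withdraws before the next visit has had no occasion to report the event, and no further data are sought afterwards. If delay does raise such events, as the Background section reports, this loss could differ between arms. The article gives nothing from which to judge its size.

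**The stated reason against the Background section.** The Safety section speaks of events arising from the intervention, and the Background section speaks of delay. The two statements can both be true. The fault is that the first is used to justify a rule covering the whole study, including the arm to which the second applies.

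**The case against.** The strongest reply is that the harms that matter most are already measured. Falls and admissions are asked about at every visit, falls and service use are listed outcomes, acute service use is kept, and between-arm differences with 95% CIs are planned. This stands. A reader might infer from the no-recording clause that harm by arm would go unreported, but the article does not support that for falls, admissions and service use among people followed up.

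A second reply is that an event causing one missed visit is not thereby lost. It can be reported at 6 months, the plan promises personal contact and efforts to locate participants, and a move into residential care is not a withdrawal. This also stands, and it confines the problem to deaths, works-related injuries of the kind described, and events that end participation. The Safety section's list is introduced as non-exhaustive, which helps a little but names no further event and no route for recording one.

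A third reply concerns size. A reader might take the 70% follow-up objective to mean that up to 30% of participants (0.30 × 40 = 12, or 0.30 × 60 = 18) could leave with a harm unrecorded. That does not follow: 70% is a minimum target, its complement is not an expected loss, and nothing suggests that every loss is caused by an event. Nor can events be counted from an assumed fall or admission rate, since the article offers none.

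Finally, an article may leave event forms and withdrawal logs to the full protocol. That would answer a silence. It does not answer an explicit statement that adverse events will not be recorded, which a fuller document would have to contradict.

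**Conclusion.** The concern holds in a limited form. The no-recording rule rests on a reason that ignores the waiting arm, and it is hard to reconcile with the sentence after it. Followed as written, it leaves three kinds of event without stated recording: deaths, injuries linked to the building work that cause no fall or admission, and events that prompt withdrawal before the next visit. It also means that the feasibility study does not try out adverse-event capture for the main trial.

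The size is qualitative. How many events would be missed among the 40 to 60 participants cannot be derived from the article, and whether the loss would be unequal between arms depends on the reported effect of delay being real. No effectiveness conclusion turns on it: the study is about feasibility, and the article treats its economic results as a guide only. The change is still worth making because it is cheap and the gap arises from the plan's own wording. The conclusion assumes that no fuller document reverses the rule.

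**What to change.** In the Safety monitoring section, delete "thus we will not record any as part of this study" and state the following instead:

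- Falls, hospital admissions, deaths, residential-care entry and injuries linked to the works are recorded, with dates, for all randomised participants in both arms.
- Recording runs up to and including any event given as the reason for withdrawal. Nothing is collected after withdrawal, which keeps the rule in the Data collection section intact.
- These events are tabulated by arm as harms and given to the existing trial advisory group.

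The section should also acknowledge that harm may arise from waiting as well as from earlier provision, so that it agrees with the Background section.

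The cost is a wording change, one log page and one table. Falls, admissions and residential-care use are already asked about at follow-up. The downside is a small reporting burden on the research team.

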## Dissemination

To the best of our knowledge, this is the first RCT of any type of housing adaptation in the UK. It is also the first RCT of bathing adaptations specifically. We believe that this is indicated due to the possible particular preventive effect which may apply to bathing adaptations specifically. Although housing adaptations have been identified as 1 of the 10 most promising prevention service for older adults,^5^ there is a paucity of high-quality evidence of prevention effect on the use of other services, particularly homecare and residential care and health and social care-related quality of life. This study will provide the foundations for a further, appropriately powered study to investigate this. The findings will be relevant to researchers, clinicians, commissioners, service users and carers.

We plan to disseminate our findings through presentations at national and international social care and occupational therapy conferences, and we will submit findings for publication in a peer-reviewed academic journal.
